#### D.6.f. Modeling study to examine the effects of multiple transmission pathways on the preventable fraction estimate.

Due to the properties of the infectious disease process discussed in Section A, it is important to assess the impact of improving water quality in the context of the multiple pathways of disease transmission. We propose to examine the preventable fraction estimates due to SODIS use, by developing and analyzing mathematical models of disease transmission in the context of the 22 villages understudy.

We will develop a standard household-level stochastic model (Ball 1999) that can be parameterized for each of the 22 villages. Four basic transmission pathways will be modeled: within household pathways that account for person-

to-person or person-to-formite-to-person transmission occurring within the household; between household or community-level pathways that account for transmission in communal settings such as schools, play areas, and bathing sites; environmental-to-person pathways that account for exposure of pathogens from environmental sources such as food and water; and person-to-environmental pathways that account for transmission of pathogens to the environment due to factors such as poor sanitation.

This modeling study will be a comparative analysis across each of the villages in the study. To this end, model parameters will be identified for each village. For example, relying on baseline survey information, the villages will be ranked with respect to hygiene and sanitation levels. These rankings will be the basis for assigning parameter values for person-to-person and person-to-environment transmission rates respectively. Once the model parameters are identified for each village, preventable fraction estimates will be obtained from the model by comparing incidence estimates under the conditions of an intervention with incidence estimates under the conditions of no intervention.

#### **D.6.g. Specimen collection and testing (stool and water specimens)**

An important component of our proposal is the collection and microbiological testing of stool specimen from study children. Data collection on pathogen-specific infections will be generated to elucidate three issues of particular interest in the current setting : i) the prevalence of asymptomatic bacterial, viral and parasitic infections in rural Bolivian children, ii) the proportion of diarrhea attributable to infection in the different treatment arms, and iii) the pathogen-specific attributable risk for diarrhea.

Prevalence of asymptomatic infection is obtained through the microbiologic testing of the random sample of 220 children at baseline. We will calculate the proportion of pathogen-positive stool samples among those children that were not classified as diarrhea. To obtain the proportion of diarrhea attributable to infection test results will be pooled from all symptomatic cases identified at baseline and at the time of their first episode. Since this will partly involve repeated measurements of the same individual we will account for the possible intra-person correlation by applying General Estimation Equation (GEE) approaches in the analysis (Zeger et al. 1988) (see also section D.9.). We will also explore how individual pathogen might be related to the probability of diarrhea.

These specimens will be tested for common causes of gastrointestinal illness due to viruses, bacteria and parasites. Stool specimens will be collected at baseline from a random sample of the children under five (N=220) and again at their first symptomatic episode later in the study. At the reviewers suggestion we will repeat testing the same cohort (regardless of disease status) at mid-point of the project. Field staff will distribute stool collection kits in the morning and collect them in the evening from the households if the child cannot produce a sample at the time of the visit. They will store the specimen in cooler boxes at 4 degrees C. and transport them to the local research office where refrigeration is possible. From there they are transferred to the central laboratory in Cochabamba within 48 hours. Participants will be notified by the study team about the test results and treatment initiated upon consultation with the medical center. A comprehensive array of tests will be performed at the Medical Faculty of the University of San Simon in Cochabamba.

Bacterial testing will be done for *Salmonella*, *Shigella*, *Campylobacter jejuni*, *Vibrio sp* and *E.coli* using standard microbiologic and biochemical tests. After biochemical identification of *E.coli* from lactose and non-lactose fermenting colonies pathogenic strains of *E.coli* (EPEC, ETEC and EIEC) will be tested for by PCR using a method co-developed by one member of our research team ([name], UCB) (Tornieporth et al. 1995).

Viral testing include rotavirus, adenovirus, astrovirus and calicivirus (Norwalk-like virus). With the exception of rotavirus, no comprehensive study of the viral origin of diarrheal illness has been undertaken in Bolivia. We will use commercially available test kits that are highly sensitive and specific: IDEIA Rotavirus, DAKO DIA rotavirus kit, Adenoclone (Meridian) an enzyme immunoassay, astrovirus will be tested using IDEIA astrovirus, DAKO DIA. Norwalk-like viruses will be tested using RT-PCR with primers developed at CDC. RNA isolation will be done by commercial kit (QUIAMP) and identification done by gel-electrophoresis and Ethidium-bromide stain. Parasitological testing will be done using SAF-fixative (sodium acetate acetic formalin) (Yang and Scholten 1977) a method that is routinely used in diagnostic laboratories in Canada and Switzerland (Marti and Koella 1993). The method does not require differential staining and has field tested in numerous of our field work in developing countries (Mausezahl 1996, Utzinger et al. 1999). *Cryptosporidium sp* will be diagnosed using a test kit (Merifluor, Meridian).

Water quality monitoring constitutes the second important component. At the *community-level* we will monitor routinely one natural water source frequented for drinking water collection in each village. Testing for fecal coliforms will be done using a portable test kit (Del Aqua kit) that is used by the Centro de Aguas y Saneamiento Ambiental. The method allows one to quantify fecal coliforms using MPN (Most Probable Number). A100 ml probe is filtered through a selective broth (Oxid's lactose sodium lauryl sulphate) and colony forming units of fecal *E.coli* are counted (Lloyd and Helmer 1991). Given the frequent identification of *Giardia lamblia* in indigenous children (Cancrini et al. 1988,

Quick et al. 1999) we will test one main water source per community qualitatively for the presence of *G.lambli*a and *Cryptosporidium* sp using the Merifluor, Meridian test kit. To correlate our findings of the viral etiologies of child diarrhea we will also test community water samples for the presence of male-specific F+RNA-coliphages. Coliphages are not only a sensitive indicator for human fecal water contamination but have also been shown to be substantially better indicators for the occurrence of viruses in water than thermotolerant coliforms or fecal streptococci (Havelaar et al. 1993). These tests will be done at the Centro de Aguas y Saneamiento Ambiental who apply a modification of the method described by Grabow *et al.* (Grabow and Coubrough 1986).

At the *household-level* the presence of fecal coliforms in stored water samples will be routinely monitored in sentinel households in villages that rank very high and low in overall reported diarrheal morbidity as established at baseline. Water samples from the 220 households selected for the baseline assessment will be collected once again at the time of a symptomatic case of diarrhea in the household. Testing for coliphages in home-stored water will only be done if a viral infection was detected in the stool specimen.

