## D.4. Definition of diarrhea (principal outcome)

An episode of diarrhea will be defined in this activity and throughout the trial as a 24 hours period with three or more non-bloody loose or liquid motions, or one or more bloody, loose or liquid motions and three diarrhea-free days between a new onset. This is in concordance with the WHO recommendations and recent research (Ahmed et al. 1994, Aziz et al. 1990, Morris et al. 1994) and allows the comparison with other studies on diarrheal diseases in developing countries. Concepts of diarrheal illness and disease differ within and between cultures (Pitts et al. 1996, Weiss 1988). For example, a nutritional program in Honduras neglected to use word 'empacho' in their instructions for correct feeding practices of diarrheal cases. The subsequent inclusion of the folk term significantly improved the program's impact (Scrimshaw and Hurtado 1988). Attempts will be made during the pilot phase to assess the cultural perception of diarrheal illness and to elucidate the folk terminology and basic local illness beliefs about diarrhea (Appendix L). We conducted similar studies in previous research to obtain and validate local folk terms for diarrheal illness that resemble most closely the biomedical definition for diarrheal illness mentioned previously (Mausezahl 1996, Pitts et al. 1996).

A start of a new episode of diarrhea will be defined as the first day of diarrhea that occurs after at least three consecutive diarrhea-free days. Similarly, the end of an episode is determined by the onset of three consecutive diarrhea-free days. Our choice of three rather than some other number of disease-free days is based on the work of Morris *et al* who modelled the sensitivity of different definitions of diarrheal episodes and described the definition we

have chosen as ideal in situations of medium to high incidence (specifically greater than six trigger events/child/year) allowing for different lengths of duration and within-child clustering (Morris et al. 1994). Persistent diarrhea is defined as an episode lasting longer than 14 days according to WHO standards (Anonymous 1988); diarrhea episodes of shorter duration will be defined as "acute".

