Additionally, stool specimens will be collected from a random sample of 220 children during the baseline morbidity surveys. In each community specimens from two children for every one-year age group will be collected (ten total per village). We will obtain one stool specimen at baseline and after 6 months, and also one specimen at the onset of their first diarrheal episode and submit it for microbiologic analysis. Stool analysis at baseline and mid-term will allow us to estimate the pathogen-specific infection rates in asymptomatic cases in both intervention arms. Microbiologic testing of stools of the same cohort will be repeated at mid-point of the project to obtain a repeated measure of infection status (regardless of disease status) at another season. By conducting microbiologic testing of the subsequent 220 symptomatic diarrhea cases we will be able to obtain rates of pathogen-specific diarrheal illnesses and pathogens responsible for the differences in diarrheal illness between intervention and control group (see section D.6g. Specimen collection and testing).

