A secondary analysis will consider estimation of the attributable fraction of diarrhea due to specific pathogens. In this case, the outcome data is the presence or absence of diarrhea among the stool samples and the explanatory variables of interest are the presence/absence of particular pathogens. In this case, we have two levels of replication: 1) the possibility of more than one stool sample (diarrhea) per child and 2) 10 children (with specimen tested) within the

cluster (village). Given the very real possibility residual correlation among the replicates, we again will use a GEE regression approach. In this case, our outcome is binary (presence/absence of diarrheal stool sample) so we will use the GEE generalization of logistic regression. We will choose the variables to adjust for (and those to consider as effect modifiers) similar to that described above (note, that treatment now plays the roll of a potential effect modifier).

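### Stools from recently ill children count as asymptomatic and serve as the non-diarrheal comparator, because no diary look-back is set; the bias is probably modest and cheap to remove

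*Protocol*

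**What the plan says.** Section D.6.g fixes the estimator: "We will calculate the proportion of pathogen-positive stool samples among those children that were not classified as diarrhea". Its source is the baseline subsample: "Prevalence of asymptomatic infection is obtained through the microbiologic testing of the random sample of 220 children at baseline". The protocol then adds a second round of stools: "we will repeat testing the same cohort (regardless of disease status) at mid-point of the project". Section D.6.b extends the estimate to that round and to the arms: "Stool analysis at baseline and mid-term will allow us to estimate the pathogen-specific infection rates in asymptomatic cases in both intervention arms".

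Section D.9 (secondary analysis) fits a GEE logistic regression in which "our outcome is binary (presence/absence of diarrheal stool sample") and pathogen presence is the explanatory variable. Non-diarrheal stools are therefore the reference.

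The only diarrhea-free interval in the protocol is the three days in section D.4, which separate episodes: "the end of an episode is determined by the onset of three consecutive diarrhea-free days". It is not applied to stools. Daily diaries with weekly visits run through the eight-week baseline (introduction, paragraph on study design and confounding) and the 12-month follow-up (section D.6.c).

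**The concern.** A stool taken shortly after an episode can still carry the agent of that episode. Under the stated rule it enters the asymptomatic group, so the prevalence mixes infection without recent illness with shedding after illness. The mixture depends on how often children fall ill, so the figure is harder to compare between villages and between the two seasons that the protocol wants to describe.

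In the D.9 regression the same stools raise pathogen detection in the reference group and pull odds ratios toward 1. Two stated aims are affected: asymptomatic prevalence, the first of the three pathogen-specific outcomes in section D.5, and the attributable fraction by pathogen. The primary outcome, diarrhea incidence, is not touched.

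**Working it through.** **The plan's own figure.** 2 children x 5 one-year age groups x 22 villages = 220 stools per round, and 220/660 = 33.3%. This agrees with the protocol. No precision is stated for the prevalence.

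**Step 1: share of well children who were recently ill.** Inputs: 5 episodes per child-year in controls and 3.33 as the target under SODIS (section D.8). Mean episode length is not given; 0 (ignored), 4 and 7 days are assumed. With exponential gaps between episodes, mean gap g = 365/rate - episode length, and share within w days = 1 - exp(-w/g).

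| Rate per year | Episode length (days) | g (days) | 7-day share | 14-day share |
|---|---|---|---|---|
| 5 | 0 | 73.0 | 9.1% | 17.5% |
| 5 | 4 | 69.0 | 9.7% | 18.4% |
| 5 | 7 | 66.0 | 10.1% | 19.1% |
| 3.33 | 0 | 109.5 | 6.2% | 12.0% |
| 3.33 | 4 | 105.5 | 6.4% | 12.4% |
| 3.33 | 7 | 102.5 | 6.6% | 12.8% |

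**Step 2: effect on prevalence.** Apparent prevalence = f x s + (1 - f) x c. Here f is the share from step 1 (9.7% to 19.1%), s is the probability that a recent-illness stool is positive, and c is the prevalence without recent illness. The protocol gives no shedding figure, so s is assumed. Section B.4 supplies values to pair within one pathogen.

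- Rotavirus: c = 13.7% (healthy controls, Brazilian study), s = 20-30%.
  - Low: 0.097 x 0.20 + 0.903 x 0.137 = 14.3%, ratio 1.04.
  - High: 0.191 x 0.30 + 0.809 x 0.137 = 16.8%, ratio 1.23.
- Astrovirus: c = 2% (healthy controls), s = 4% (detection in acute diarrhea, every case assumed still shedding).
  - Low: 0.097 x 0.04 + 0.903 x 0.02 = 2.19%, ratio 1.10.
  - High: 0.191 x 0.04 + 0.809 x 0.02 = 2.38%, ratio 1.19.

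**Step 3: effect on the odds ratio.**

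- Rotavirus, 30.6% in cases against 13.7% in controls (same Brazilian study): OR = (0.306/0.694)/(0.137/0.863) = 2.78. With the comparator at 14.3% to 16.8% it becomes 2.64 to 2.18.
- Astrovirus, 4% against 2%: OR 2.04 becomes 1.86 to 1.71.

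**Step 4: arm difference at mid-term.** Take an adverse case: equal carriage of 3%, s = 30%, 4-day episodes.

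- 14-day window: control 0.183 x 0.30 + 0.817 x 0.03 = 7.9%; intervention 0.123 x 0.30 + 0.877 x 0.03 = 6.3%. Difference 1.6 points.
- 7-day window: control 0.097 x 0.30 + 0.903 x 0.03 = 5.6%; intervention 0.065 x 0.30 + 0.935 x 0.03 = 4.8%. Difference 0.8 points.

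With about 100 symptom-free stools per arm (assumed, out of 110), the standard error of the difference is sqrt[(0.079 x 0.921 + 0.063 x 0.937)/100] = 3.6 points, or 3.1 points for the 7-day case, before clustering. The artificial difference is 0.44 and 0.25 standard errors.

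**The case against.** **A recovered child who still excretes is infected without symptoms.** That fits the literal term, and the protocol does not speak of carriage. If SODIS prevents episodes and hence later excretion, a lower figure is a real effect. This stands, so the overall figure should be kept and the split added. It does not rescue the D.9 comparator, where stools after recent illness blur the contrast being estimated.

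**The diaries are already to be linked to stools.** The introduction's paragraph on microbiological testing says that stool results will be correlated with diary symptoms. It sets no look-back and does not change the D.6.g rule.

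**Stronger readings that the documents do not support:**

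- *Days without diarrhea inside an episode also count as asymptomatic.* Under section D.4 a child on a one- or two-day gap is still in an episode. D.6.g does not say when status is judged, but a child four days past the last diarrhea day counts as asymptomatic on either reading.
- *Prevalence is inflated about two-fold or more.* That requires pairing 3% adenovirus detection in asymptomatic children with a shedding share taken from rotavirus detection in patients (22.5% and 42% in two hospital sources), held flat for up to 14 days. These are different pathogens, and detection during illness is not shedding after it.
- *The headline prevalence is biased between arms.* D.6.g bases it on baseline stools, taken before SODIS starts.

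**Conclusion.** The point holds as a modest, avoidable bias. The rule admits recently ill children to the asymptomatic group and to the D.9 comparator, and nothing in the protocol removes them. At 5 episodes per child-year they make up about 9-10% (7 days) or 17-19% (14 days) of well children; at 3.33 the shares are about 6-7% and 12-13%.

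With figures matched by pathogen, prevalence is inflated about 1.04 to 1.23 times, and a rotavirus odds ratio of 2.78 would read 2.64 to 2.18. This rests on assumed episode lengths, assumed shedding, and the cited healthy-control figures standing in for prevalence without recent illness. The effect is larger only where carriage is very low and shedding common, and small for the long-lived parasites that dominated the pilot stools. Any arm difference is confined to mid-term and is under half a standard error even in the adverse case.

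**What to change.** In sections D.6.g, D.6.b and D.9, use the diary to split symptom-free stools into two classes: no diarrhea in the preceding 7 days, and recent diarrhea.

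- Report asymptomatic prevalence overall and for each class.
- Use only the first class as the main comparator in D.9. As sensitivity analyses, use all non-diarrheal stools and, where the diary is long enough, a 14-day window.
- Collect baseline stools after at least 7 diary days, or 14 if that window is to be used at baseline.
- Do not exclude children because an episode starts after the stool; that conditions on the future.

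**Cost.** About 10% of symptom-free stools leave the main comparator, up to 19% with 14 days. If 75% of the 220 children are well, as in the pilot, that is about 15-17 of 165 (0.091 to 0.101 x 165), or 29-32 with 14 days. They are still reported. At mid-term slightly more leave in the control arm, so the arm comparison should also be shown for all non-diarrheal stools. The baseline stool date must be set in the field plan; otherwise the change uses data already collected.

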- *Health outcome and stool laboratory* : In total, 35 (24.6%) of the children were reported experiencing an episode of diarrhea at the time of the interview. The frequency of reported diarrhea steadily decreased from 35.1% in infants (defined as <12 months for this analysis) to 0% in children below 5. ( $p=0.016$ ) (Appendix F, Table below). We successfully obtained stool samples of 80 children and completed microbiological testing in 74 (92.5%) of them (see also Appendix F, Table 2/3.). Bacterial infections were found in 5 children (Salmonella sp 2x, Shigella 1x, E.coli 2x). Protozoal and helminthic infections were recorded in 48.6% (36/74) and less often in symptomatic cases than in asymptomatic cases (OR=0.3, CI=0.08 – 1.11). Diagnostic procedures may explain this finding: 94% of the stool samples of symptomatic children were recorded as liquid in the laboratory. However, same aliquots of liquid and solid fecal matter were used for stool microscopy rendering liquid and thus, diluted stool samples less likely for parasite detection.

Reported child diarrhoea and parasitic infection status of 140 children <5 years from Mizque, Bolivia; 2001

|                                  | Total      | Children's age (months) |           |           |          |         |
|----------------------------------|------------|-------------------------|-----------|-----------|----------|---------|
|                                  |            | 0-11                    | 12-23     | 24-35     | 36-47    | 48-60   |
| Reported diarrhoea status |            |                         |           |           |          |         |
| - Diarrhea                       | 35 (25%)   | 20 (35.1)               | 12 (30)   | 3 (13.6)  | (0)      | (0)     |
| - No Diarrhea                    | 105 (75%)  | 37 (64.9)               | 28 (70)   | 19 (86.4) | 13 (100) | 8 (100) |
| Total                     | 140 | 57                      | 40        | 22        | 13       | 8       |
| Stool diagnostics         |            |                         |           |           |          |         |
| - Entamoeba hist./dispar  | 17 (23.0%) | 2 (7.4)                 | 6 (27.3)  | 4 (26.6)  | 2 (33.3) | 3 (60)  |
| - Giardia lamblia         | 23 (31.1%) | 1 (3.7)                 | 6 (27.3)  | 9 (60)    | 3 (50)   | 4 (80)  |
| - Protozoa                       | 34 (45.9%) | 3 (11.1)                | 10 (45.5) | 12 (80)   | 5 (83.3) | 4 (80)  |

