## D.5. Evaluation of the outcome measures

Evaluation of differences in the primary outcome measure between the active and control arms will be through relative incidence rates of gastrointestinal illness (total episodes of child diarrhea / total person-time of observation in the control group divided by the same measure in the active group) adjusted for the nature of the cluster sampling. Secondary outcomes include child-level outcome measures such as the total number of days with diarrhea, the mean duration of diarrhea, and the number of visits to health care providers caused by the diarrhea. We also will obtain information to allow an analysis using a combination of symptoms that describe 'highly credible gastrointestinal illness' (HCGI) (Payment et al. 1991) from our weekly diarrhea monitoring household interviews (Appendix J).

Outcome data will be collected through a surveillance system established to measure diarrheal morbidity through daily illness diaries kept by the mother/caretakers of the children, and through weekly home-visits by project staff. A standardized questionnaire will be administered covering the clinical signs and gastrointestinal symptoms of current illness. Environmental (household and village-specific characteristics) as well as behavioral traits (water and food handling practices in the home, presence of pets, latrine arrangements) will also be recorded. Weekly home visits result in a total of 52 environmental and morbidity recording sheets for each child in the study.

Stool specimens will be collected and submitted for microbiologic analysis from a sub-sample of 220 (33%) of the children in the study during baseline, at their first diarrheal episode. In addition, as suggested by the reviewer, the entire sub sample will also be re-examined at a fixed time (at 6 months of follow up). This will allow us to measure three additional pathogen-specific outcomes: the prevalence of asymptomatic infections; the proportion of diarrhea attributable to infection for each organism detected in the study; and differential (pathogen-specific) infection rates in intervention and control group.

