#### **D.6.b. Baseline morbidity surveys in the trial villages to estimate the period prevalence of diarrheal episodes in children <5 years and to facilitate randomization of communities**

At the beginning of the study, a prospective eight week survey among households with children <5 years will be conducted in the 22 villages to estimate the proportion (period prevalence) of child diarrheal illness. The usually short duration of a diarrheal episode and the short incubation period for a new episode will allow us to estimate the incidence density of child diarrhea in each cluster (i.e. village-cluster incidence rate) at baseline. The main purpose of obtaining a prevalence estimate is to facilitate matching of study sites according to the occurrence of reported diarrhea in children. This change (previously a 7 day cross-sectional survey but now an eight week longitudinal measurement) was done in order to address a comment in the prior review about improving our strategy to minimize possible differences in confounding factors between villages at baseline. Sites ranked by eight week baseline diarrhea rates are then grouped in pairs and the introduction of the SODIS intervention is randomly allocated to one of them. Thus, 11 sites receive the intervention, 11 other sites serve as controls. This high level randomization of the village-clusters to the SODIS intervention is the single most effective strategy to limit bias in the estimation of the intervention effect (Murray 1998) (cf. also Section D.7.). PCI will adapt to the random allocation of the SODIS intervention and will start activities in the villages of the intervention arm after our baseline survey has been completed.

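### The arm-specific proportion of diarrhea attributable to infection pools cases from before SODIS began with follow-up cases, which shrinks the arm difference in that secondary measure

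*Protocol*

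**What the plan says.** Protocol D.6.g sets three goals for the stool testing. The second is "the proportion of diarrhea attributable to infection in the different treatment arms". The introduction to the revised application, under microbiological testing, also gives this aim by arm. The next paragraph of D.6.g gives the method: "test results will be pooled from all symptomatic cases identified at baseline and at the time of their first episode". It adds that repeated specimens from one child will be handled by GEE and refers to D.9. The first-episode specimens belong to follow-up, since the sampled children are tested at baseline and "again at their first symptomatic episode later in the study".

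D.6.b fixes the order of events. The eight-week baseline survey comes first. "Sites ranked by eight week baseline diarrhea rates are then grouped in pairs", and one village of each pair is then randomly allocated to SODIS. The implementing organisation "will start activities in the villages of the intervention arm after our baseline survey has been completed".

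The specimens come from a "sub-sample of 220 (33%) of the children in the study" (D.5). On sampling, D.6.b says: "In each community specimens from two children for every one-year age group will be collected (ten total per village".

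**The concern.** The target is a proportion in each arm, but part of the data predates the arms. A symptomatic child sampled at baseline in a village later allocated to SODIS has had no SODIS. Counting that child in the intervention arm mixes untreated time into the treated group, and the control arm receives a similar set of cases. Both arm estimates are then pulled toward a common baseline value.

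GEE for correlation within a child affects the standard errors and the weighting of observations. It does not separate baseline from follow-up. D.9 treats treatment as a potential effect modifier in the attributable-fraction model and names no term for period.

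At stake is one secondary result: whether the infectious share of diarrhea differs between the arms. The rule as written would understate such a difference.

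**Working it through.** **1. The plan's own figure.** Two children × 5 one-year age groups × 22 villages = 220, and 220/660 = 33.3%. The stated subsample reproduces, with 110 children per arm.

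**2. Formula.** Let B be the baseline symptomatic cases, F the first-episode cases in follow-up, and w = B/(B+F). If the baseline infection share is the same in both arms in expectation, and w is about equal in both:

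pooled arm difference = (1 − w) × follow-up arm difference.

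The relative shrinkage is w, whatever the true shares are.

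**3. Number of first episodes (assumption).** I take F = 220, one per sampled child. A Poisson model at the D.8 rates gives nearly the same: 110 × (1 − e^−3.33) ≈ 106 in the SODIS arm and 110 × (1 − e^−5) ≈ 109 in the control arm. Fewer first episodes would make w larger.

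**4. Number of baseline cases (assumption).** The protocol gives none, so I show a range.

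- *Age-standardised pilot.* The C.1 table gives 20/57, 12/40, 3/22, 0/13 and 0/8 by year of age. With equal weights the mean is (0.351 + 0.300 + 0.136 + 0 + 0)/5 = 0.157, so B = 220 × 0.157 ≈ 35.
- *Crude pilot.* In C.1, "35 (24.6%) of the children were reported experiencing an episode of diarrhea at the time of the interview". Among children with a tested stool it was 18/74 = 24.3%. B ≈ 54.
- *National two-week prevalence* (B.4), 29.9%: B ≈ 66.
- *Upper case.* One case per affected child over all eight baseline weeks, Poisson at 5 per year: 220 × (1 − e^(−5×8/52)) ≈ 118.

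**5. Results.**

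| Basis for B | B | w = B/(B+220) |
|---|---|---|
| Pilot, age-standardised | 35 | 14% |
| Pilot, crude | 54 | 20% |
| National two-week prevalence | 66 | 23% |
| Eight-week Poisson (upper case) | 118 | 35% |

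The pilot sample was weighted to infants (57 of 140), while the trial samples the age groups equally. The age-standardised row therefore fits the planned subsample better than the crude row.

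**6. Do the extra cases make up for the dilution?** No. With similar variances the test statistic scales with (1 − w) × √(1/(1 − w)) = √(1 − w). That is 0.93 for w = 14%, 0.90 for 20% and 0.88 for 23%.

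**7. Illustration only.** The protocol gives no infection shares by arm and no power for this measure. Assume 50% in control and at baseline, 30% under SODIS, a two-sided 5% test of two proportions, and no allowance for clustering. Follow-up cases alone give a 20-point difference and 86% power. Pooling gives 17.3, 16.1, 15.4 and 13.0 points for the four rows above, with power of 80%, 77%, 75% and 68%.

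**The case against.** It can be said in the plan's favour that the pooling sentence does not repeat the reference to arms. D.5 lists a proportion attributable to infection for each organism with no arm in it, and lists infection rates by arm as a separate outcome. For an overall aetiologic fraction, pooling baseline and follow-up cases is ordinary use of the data. This supports pooling for an overall estimate. It does not rescue D.6.g, where the aim is stated by arm and no other method is given for it.

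Three limits stand.

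- A reader might infer that every SODIS effect on pathogens is diluted. The protocol does not support that. D.6.b draws its comparison of the pathogens behind the between-arm difference from the subsequent symptomatic cases, which are follow-up cases only.
- A reader might infer that a planned test loses a known amount of power. No test or power is stated for this proportion, the introduction speaks only of describing it, and the model in D.9 does not take treatment as its main contrast. Power figures can only be illustrative.
- A reader might take 20% as the settled size. That rests on the infant-heavy pilot sample. The age-standardised figure is about 14%, and all the figures depend on assumed case counts.

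A period term could be added in a statistical analysis plan that is not shown. However, the protocol has not left this open: it states the pooling rule.

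**Conclusion.** The point holds for the arm-specific proportion in D.6.g. As written, the rule includes cases from before allocation and before SODIS in an arm contrast, and the expected arm difference shrinks by the baseline fraction of pooled cases. That is about 14% to 23% on the pilot and national rates, and about 35% if one case per affected child over the whole baseline survey is counted.

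This rests on about 110 first episodes per arm, on assumed numbers of baseline cases, and on equal baseline shares between arms in expectation. A chance imbalance at baseline could move a given estimate either way.

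The effect is moderate and confined to a secondary measure in a one-third subsample. The primary incidence comparison is not affected.

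**What to change.** In D.6.g, state that the arm-specific proportion is estimated from post-allocation first-episode specimens only. Alternatively, keep both sets of cases in the model with a period term and an arm-by-period term, and report the follow-up contrast. Use baseline symptomatic cases only for an overall estimate or a pre-intervention estimate for both arms combined.

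Reconcile D.6.g with D.6.b, so that both between-arm pathogen questions use the same follow-up cases.

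The cost is a sentence or two of text and no new data. The arm-specific estimate would rest on fewer specimens, but the dropped ones carry no information on the effect of SODIS.
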